### Intervention Algorithm

Therapeutic decisions in the study are guided by an algorithm based on C-peptide and GADAb levels (Figure 1). Patients with a C-peptide level below 0.3 nmol/L and positive GADAb are considered suspected type 1 diabetes cases; they continue MDI and CGM and are referred for specialized care. Those with similarly low C-peptide levels but negative GADAb also continue MDI and CGM with no changes in treatment.

For patients with intermediate C-peptide values (0.3‐0.7 nmol/L), the approach varies based on GADAb status. If GADAb is positive, treatment remains unchanged with continued MDI and CGM. However, if GADAb is negative, clinicians consider discontinuing prandial insulin and introducing noninsulin hypoglycemic agents as appropriate.

Participants with C-peptide levels above 0.7 nmol/L regardless of GADAb status are also considered for discontinuation of prandial insulin and initiation of noninsulin therapies. In individuals who discontinue prandial insulin, CGM use is typically discontinued as well as they do not meet the criteria for public funding [26].

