### Sample Size and Statistical Analysis

At the time of the study planning, data from the Lleida health care region had identified 1388 people with T2DM treated with MDI. On the basis of prior clinical experience, approximately 25% of these individuals may have sufficient residual β cell function to discontinue prandial insulin. To estimate this proportion with a 95% CI and a margin of error of –5% to +5%, a sample size of 239 participants was estimated.

The study population will be characterized at baseline with respect to age, BMI, duration of diabetes, presence of chronic diabetes-related complications (microvascular and macrovascular), and cardiovascular risk factors. In addition, in-depth phenotyping will be performed using the homeostatic model assessment of β cell function and homeostatic model assessment of insulin resistance indexes [27] and GADAb measurements.

For the primary outcome, the proportion of participants who discontinue prandial insulin after the application of the diagnostic algorithm and sustain this change over a 6-month follow-up period will be calculated, along with its corresponding 95% CI.

Secondary outcomes will include measures of glycemic control, patient-reported outcomes, and safety outcomes. Glycemic control will be assessed using HbA_1c_ and CGM-derived metrics, including time in range (70‐180 mg/dL), time below range, time above range, mean glucose, and glycemic variability indexes. Patient-reported outcomes will include validated scores for treatment satisfaction, adherence, and quality of life analyzed according to each instrument’s scoring manual. Safety outcomes will include the incidence of severe hypoglycemia.

To evaluate changes over time (eg, from baseline to follow-up visits), paired 2-tailed *t* tests or Wilcoxon signed-rank tests will be used depending on data distribution. Between-group comparisons (eg, discontinuation vs continuation of prandial insulin) will be conducted using Student *t* tests or Mann-Whitney *U* tests as appropriate, as well as using linear mixed-effects models to account for within-subject correlation.

For categorical secondary outcomes, including severe hypoglycemia, comparisons between groups will be performed using chi-square or Fisher exact tests as appropriate. For outcomes measured repeatedly across follow-up visits, analyses will be conducted using linear mixed-effects models.

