### Limitations

This study has several limitations. First, as with many observational studies involving voluntary participation, there is potential selection bias. Individuals who choose to participate may differ systematically from those who do not, for example, by being more motivated, having greater health literacy, or exhibiting more stable diabetes management. Such characteristics could affect adherence, clinical outcomes, and openness to treatment simplification, thereby potentially limiting the generalizability of the findings [21].

Second, although the study includes all persons with a diagnosis of T2DM treated with MDI within the participating centers, recruitment depended on the initiative of local primary care teams, which may introduce variability in enrollment rates and patient selection. Third, the intervention algorithm offers flexibility in its clinical application, potentially leading to deviations from the proposed protocol. However, given the pragmatic nature of the study, this flexibility is considered necessary to ensure patient safety and adapt the intervention to the heterogeneous clinical profiles of T2DM, a condition influenced by multiple factors affecting treatment response. Lastly, the duration of diabetes may affect the reliability of autoantibody testing. In long-standing cases, GADAb titers may decline over time, leading to false-negative results. Although longitudinal data are limited, up to 40% of GADAb-positive patients may become seronegative 10 years after diagnosis [29]. Despite this, GADAb was selected over other autoantibodies due to its higher prevalence and persistence in patients with LADA [5].

In summary, these limitations—including the use of convenience-based recruitment, potential selection bias, variability in recruitment across centers, and the pragmatic flexibility of the intervention algorithm—should be considered when interpreting the findings. These factors may limit causal inference and applicability, but they are consistent with the study’s feasibility-focused, real-world nature.

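### The secondary comparison of people who stop and people who continue prandial insulin uses unadjusted tests, although C-peptide, GADAb and clinician judgement form the groups

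*Protocol article*

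**What the plan says.** The Sample Size and Statistical Analysis section names the comparison and its tests: "Between-group comparisons (eg, discontinuation vs continuation of prandial insulin) will be conducted using Student" t tests or Mann-Whitney U tests, "as well as using linear mixed-effects models to account for within-subject correlation". For categorical secondary outcomes, severe hypoglycemia among them, "comparisons between groups will be performed using chi-square or Fisher exact tests as appropriate". No covariate is named for any of these.

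The Intervention Algorithm section says how the groups arise: "Therapeutic decisions in the study are guided by an algorithm based on C-peptide and GADAb levels". With C-peptide below 0.3 nmol/L nobody is moved off multiple daily injections. GADAb-positive people are also referred, and for the rest: "Those with similarly low C-peptide levels but negative GADAb also continue MDI and CGM with no changes in treatment". In the 0.3 to 0.7 range, positive GADAb again means no change, but "if GADAb is negative, clinicians consider discontinuing prandial insulin and introducing noninsulin hypoglycemic agents as appropriate". Above 0.7 nmol/L, discontinuation is considered whatever the GADAb result.

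The Limitations section adds that "the intervention algorithm offers flexibility in its clinical application, potentially leading to deviations from the proposed protocol".

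**The concern.** The two groups are not exchangeable. They differ by design in β cell reserve and autoimmunity. Among those the algorithm allows to stop, they also differ by whatever led the clinician to act or not. A t, Mann-Whitney, chi-square or Fisher test takes none of this into account. The mixed models, as described, deal with repeated measurements on one person, which is a different problem from differences between the people in each group.

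There is also a lack of overlap. In the strata that the algorithm keeps on prandial insulin there is nobody to compare with, so even a covariate-adjusted model fitted to everyone would have to extrapolate there.

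What is at stake is the reading of secondary results on HbA1c, patient-reported outcomes and severe hypoglycemia. A difference between stoppers and continuers, or the absence of one, could come entirely from who was selected. This matters because the Discussion says the study will assess whether prandial insulin can be safely removed.

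**Working it through.** **1. The plan's own figure.** Inputs from the sample size section: expected proportion 0.25, margin 0.05, 95% confidence, population 1388.

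- n0 = 1.96² × 0.25 × 0.75 / 0.05² = 288.1
- with finite population correction: 288.1 / (1 + 287.1/1388) = 238.7, rounded up to 239

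The stated 239 is reproduced. It is sized for one proportion, and the comparison of stoppers with continuers played no part in it.

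**2. Where both treatment choices can occur**, from the Intervention Algorithm section:

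| C-peptide (nmol/L) | GADAb | Algorithm | Discontinuers available |
|---|---|---|---|
| below 0.3 | positive | stay on prandial insulin, refer | none |
| below 0.3 | negative | stay on prandial insulin | none |
| 0.3 to 0.7 | positive | stay on prandial insulin | none |
| 0.3 to 0.7 | negative | stopping considered | yes |
| above 0.7 | either | stopping considered | yes |

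Three of the five rows contribute only to the continuation group.

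**3. False-positive rate when the groups differ by selection alone.** Assume that 25% of 239 stop, which gives 60 versus 179, that stopping has no effect, and that selection shifts the outcome by b standard deviations. The documents give no value for b, so a range is shown.

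- SE = √(1/60 + 1/179) = 0.149
- P(reject) = 1 − Φ(1.96 − b/SE) + Φ(−1.96 − b/SE)

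| b (SD) | b/SE | P(reject) |
|---|---|---|
| 0 | 0 | 5% |
| 0.1 | 0.67 | 10% |
| 0.2 | 1.34 | 27% |
| 0.3 | 2.01 | 52% |
| 0.5 | 3.35 | 92% |

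**4. How C-peptide alone could produce such a shift.** This was simulated with 2000 runs per setting, under these assumptions: n = 239, only the upper half of C-peptide is eligible, a random half of those stop (25% overall), stopping has no effect, and outcome and C-peptide correlate at ρ. The mean standardized C-peptide is 0.798 in stoppers and −0.798 × 0.25/0.75 = −0.266 in the rest, so the expected outcome difference is 1.064 × ρ SD.

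| ρ | Expected difference (SD) | t test | Mann-Whitney | Linear model with C-peptide |
|---|---|---|---|---|
| 0 | 0 | 5.6% | 5.7% | 5.2% |
| 0.1 | 0.11 | 10.8% | 10.4% | 5.8% |
| 0.2 | 0.21 | 28% | 27.5% | 4.8% |
| 0.3 | 0.32 | 60% | 56.6% | 6.8% |
| 0.5 | 0.53 | 97% | 95.9% | 5.4% |

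The last column is a best case. The fitted model is the one that generated the data, so its true rate is 5% and the scatter is simulation error. Clinician choice was also made random within the eligible half. Real clinician choice may depend on other prognostic factors, which adjustment for C-peptide alone would miss.

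**The case against.** The strongest reply is that the contrast is peripheral. The primary outcome is a single proportion with a confidence interval, the design uses each person as their own control, and the glycemic and patient-reported outcomes are framed as changes from baseline. Stopping versus continuing appears only as an example in the analysis section. All of that stands, and it limits the reach of this point.

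A second reply is that mixed models are planned too, and that a full analysis plan may list their covariates. In part this holds. A mixed model of baseline and follow-up values does use the baseline outcome, so the complaint about ignoring baseline applies only to the simple tests. But the article itself commits to those tests, and the one purpose it gives for the mixed models does not address confounding.

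A third is that the Limitations section already says causal inference may be limited. That remark refers to volunteer selection, variation between centers and flexible use of the algorithm. It does not mention confounding between the two treatment groups, and it changes no analysis.

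A reader might go further and infer that the groups will be formed by month-6 status, so that people who stop and then restart are counted as continuers and stopping looks better than it is. The documents do not say this. Study Procedures and Timeline puts the decision at visit 1, and the primary outcome separates stopping from remaining off at the final visit. The direction of any such distortion would also depend on what restarting does to HbA1c by month 6. The fair observation is only that the article does not say which time point defines the groups.

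**Conclusion.** The point holds for the secondary between-group comparisons and no further. As written, they are confounded by indication, and in three of the five algorithm strata there is no discontinuer to compare with, apart from the deviations that the article expects. With 60 versus 179 participants and no treatment effect, a selection difference of 0.1 to 0.5 SD would give a significant result 10% to 92% of the time. Those shifts, the 25% who stop and the correlations in the simulation are all assumptions, so the figures show sensitivity and do not forecast this study's bias.

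Two stronger readings are not supported. The primary proportion and the within-person changes do not use this contrast and are not affected. The article also does not state that the contrast will be presented as the causal effect of stopping prandial insulin. The risk is that an unadjusted P value will be read that way. It should be corrected in the analysis wording and does not threaten the main result.

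**What to change.** - **Population.** Restrict the contrast to participants whom the algorithm makes eligible for stopping: C-peptide above 0.7 nmol/L, or 0.3 to 0.7 with negative GADAb. Report the ineligible strata separately and descriptively.
- **Groups.** State that they follow the visit 1 decision. Table 1 lists pharmacological treatment only at visits 0 and 2, so confirm that the decision can be taken from the treatment record.
- **Continuous outcomes with a baseline value.** Replace the unadjusted tests with one regression or mixed model, adjusted for the baseline outcome, C-peptide and clinical covariates such as diabetes duration, BMI and eGFR.
- **DTSQc.** It is collected only at the final visit, so use the same covariates without a baseline value.
- **Severe hypoglycemia.** Use a covariate-adjusted model if there are enough events, and otherwise describe it. Allow for the 12-month window before enrollment against 6 months of follow-up, for example by using rates.
- **Label.** Call the contrast associational. Note that CGM usually ends when prandial insulin is stopped, so the groups also differ in CGM use, which these covariates cannot separate from stopping insulin.

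The covariates are already collected and no treatment rule changes, so the cost is in analysis wording and precision. In the illustration above, restriction leaves about 60 versus 60. The SE becomes √(1/60 + 1/60) = 0.183 against 0.149, about 22% larger (0.183/0.149 = 1.22) before any gain or loss from covariates. Confounding by unmeasured reasons for the clinician's choice remains. The wording should be settled before the outcome data are examined, if that is still possible.

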CGM variables will also be examined as potential predictors of pancreatic reserve and insulin resistance. Depending on whether outcomes are continuous or categorical, linear or logistic regression models will be applied. Results will be expressed as regression coefficients or odds ratios with corresponding 95% CIs.

Loss to follow-up will be quantified and reported as the proportion of participants without outcome data at each follow-up time point. When available, reasons for loss to follow-up will be documented. Baseline characteristics of participants with complete follow-up and those lost to follow-up will be compared to assess potential differential attrition. A complete-case analysis will be used as the primary analytical approach when the proportion of missing data is low, and missingness will be considered compatible with a missing completely at random mechanism. To account for potentially informative missingness, multiple imputation by chained equations will be performed under a missing-at-random assumption, including all variables used in the main analyses and auxiliary variables related to missingness.

All statistical analyses will be performed using the R software (version 4.1.2; R Foundation for Statistical Computing), with a 2-sided *P* value of <.05 considered statistically significant.

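### Between-group mean comparisons should use Welch's t test: at the planned split of about 60 versus 179, a pooled-variance Student test keeps its 5% level only if the two groups have equal spread

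*Protocol article*

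**What the plan says.** In the protocol article, Sample Size and Statistical Analysis, the rule for comparing groups is: "Between-group comparisons (eg, discontinuation vs continuation of prandial insulin) will be conducted using Student" t tests or Mann-Whitney U tests, whichever is appropriate, "as well as using linear mixed-effects models to account for within-subject correlation". No assumption about the variances is stated. Results are judged at a "2-sided *P* value of <.05 considered statistically significant".

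The expected group sizes follow from the planning values in the same section: "approximately 25% of these individuals may have sufficient residual β cell function to discontinue prandial insulin", and a "margin of error of –5% to +5%, a sample size of 239 participants was estimated". The primary outcome is one proportion with its 95% CI and uses none of these tests.

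The Intervention Algorithm section shows how the groups arise. C-peptide and GADAb determine who is considered for stopping prandial insulin, and the clinician then decides.

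**The concern.** Student's t, as the name is normally understood, pools the two variances. With equal group sizes that does little harm. With one group about three times the other, the pooled variance is dominated by the larger group, so the standard error is wrong whenever the spreads differ. It is too small if the smaller group varies more and too large if it varies less.

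Unequal spread is plausible here. The groups are selected on beta-cell function, autoimmunity and clinical judgment, and they are treated differently afterwards. Some between-group statements on glycemic control and patient-reported outcomes could then carry P values that do not have their nominal meaning, in a direction that cannot be known in advance.

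**Working it through.** **Inputs.** From Sample Size and Statistical Analysis: expected proportion 25%, margin 5 points, 95% CI, population 1388, sample size 239, two-sided 5% level. Assumed, because the article gives none: the ratio r of the discontinuers' SD to the continuers' SD.

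**The plan's own figure.** n0 = 1.96² × 0.25 × 0.75 / 0.05² = 288.1. With the finite population correction, 288.1 / (1 + 287.1/1388) = 238.7, which rounds up to 239. The stated sample size reproduces.

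**Group sizes.** 0.25 × 239 = 59.75, so about 60 discontinue and 179 continue, a ratio of 1:2.98. This split is inferred from the planning value.

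**Large-sample error of the pooled test.** Set the continuers' SD to 1.

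- Variance the test uses: P = [(59r² + 178)/237] × (1/60 + 1/179)
- True variance of the difference: T = r²/60 + 1/179
- Type I error = 2 × [1 − Φ(1.96 × √(P/T))]

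For r = 1.5:

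- P = (310.75/237) × 0.02225 = 0.02918
- T = 0.0375 + 0.00559 = 0.04309
- √(P/T) = √0.677 = 0.823, and 1.96 × 0.823 = 1.613
- Two-sided error = 0.107

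**Results at 60 versus 179**, true difference zero. Simulation: normal data, 20,000 runs per row.

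| SD ratio r (assumed) | Pooled t, formula | Pooled t, simulated | Welch, simulated |
|---|---|---|---|
| 0.67 | 1.8% | 1.9% | 5.1% |
| 0.8 | 2.9% | 2.8% | 4.8% |
| 1 | 5.0% | 5.1% | 5.1% |
| 1.25 | 7.9% | 7.9% | 4.9% |
| 1.5 | 10.7% | 11.1% | 5.4% |
| 2 | 15.1% | 15.2% | 4.9% |

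**Sensitivity.**

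- Near-equal groups (120 versus 119): the pooled test stays at 4.9% to 5.1% for SD ratios from 0.5 to 2. Imbalance and unequal spread are both needed for harm.
- Other splits at r = 1.5: 12.1% if 20% discontinue (48 versus 191), and 8.1% if 35% do (84 versus 155).
- Skewed data at 60 versus 179, r from 0.67 to 1.5: Welch gives 4.6% to 5.8%.
- Equal SDs: Welch costs about 0.4 points of power, at a power of about 76%.

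**The case against.** The strongest reply is that no defect has been shown. The article gives no SDs, and with equal spread the test holds its level even at 1:3. That is correct, so the error rates above are conditional.

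A reader might infer that discontinuers must vary more because their treatment changes, and hence that false positives are raised. The article does not support that direction. Continuers are a mixed group: low C-peptide with either GADAb status, intermediate C-peptide with positive GADAb, and candidates whose clinician did not stop prandial insulin. Under Study Outcomes they are also studied for the effect of CGM. They may well vary more, and the pooled test would then be conservative. Welch is preferable in either case.

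A reader might also extend the criticism to the before-after tests, where the plan says "Wilcoxon signed-rank tests will be used depending on data distribution", and infer that the switch occurs exactly when the signed-rank test fails. It does not. Modelling the switch as a Shapiro-Wilk test at 5% (the article names none), heavy-tailed symmetric changes trigger it in 72% to 100% of simulated runs with the error at 5.2% to 5.3%. Skewed measurements that are exchangeable before and after give 4.7% to 5.4%. Inflation for the mean does appear when the changes themselves are skewed (9.4% at n = 60 and 22.9% at n = 239, for skewness 1). Whether the mean is the right target for such measures is a choice of estimand on which statisticians differ. The wording about the data distribution also belongs to the paired tests only and does not govern the between-group rule.

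A third inference would be that the plan leaves competing results for one contrast with no ruling. The same section goes on to assign repeatedly measured outcomes to linear mixed-effects models, and any remaining hierarchy is detail that an article commonly leaves to a fuller document.

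Two further points stand. "Pooled" is a reading of the name Student, since the text states no variance assumption. And 60 versus 179 may not apply to 6-month CGM contrasts, because the Intervention Algorithm section says CGM is typically stopped along with prandial insulin. The test is nevertheless named in the article, so asking for a better one is not a complaint about missing detail.

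**Conclusion.** The point holds in a limited form. For nonrandomized groups expected at about 1:3, the named Student test is a weaker choice than Welch's because its true level depends on an SD ratio that nobody knows beforehand: from about 2% at a ratio of 0.67 to about 15% at a ratio of 2, against about 5% for Welch across that range. This rests on three assumptions: that Student means the pooled-variance test, that about 25% discontinue, and that the spreads differ, which is plausible but undocumented. The documents do not show that error rates will in fact be wrong, or in which direction. Only secondary between-group comparisons are touched; the primary proportion, its interval and the sample size of 239 stand.

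**What to change.** In Sample Size and Statistical Analysis, replace Student t tests with Welch's unequal-variance t test for between-group mean comparisons. If the unequal-variance form was already intended, say so.

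The cost is one phrase, no new data and no change in sample size. The power loss is negligible, about 0.4 points, if the variances turn out equal. The article places formal analysis after the end of follow-up, so the wording should be settled before results are seen.

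Optional, and not corrections of an error: give the mean change with a 95% CI alongside any signed-rank result, and name one reported result for each between-group outcome.

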### Study Outcomes

We defined the primary study outcome as the proportion of participants in whom prandial insulin is successfully discontinued after the application of the therapeutic algorithm and who remain without prandial insulin at the final visit (6 months).

Secondary outcomes encompass several domains. Glycemic control following therapeutic optimization is evaluated through changes in HbA_1c_ and CGM-derived metrics, including time in range and time below range. Patient-reported outcomes are also assessed by comparing changes from baseline to 6 months after the intervention, including changes in quality of life (using the Diabetes Quality of Life Questionnaire), treatment satisfaction (using the Diabetes Treatment Satisfaction Questionnaire, both status and change versions), medication adherence (measured using the Adherence to Refills and Medications Scale), and physical activity levels (evaluated using the Spanish version of the International Physical Activity Questionnaire).

Safety outcomes include the number of severe hypoglycemic episodes at the final visit 6 months after the intervention compared with the 12-month period before enrollment. The study also examines the predictive value of CGM metrics by analyzing their association with pancreatic reserve and insulin resistance considering both continuous and categorical variables.

Finally, among patients who continue prandial insulin and CGM use for 6 months, the study assesses the impact of CGM on glycemic control (HbA_1c_ and CGM metrics), as well as changes in quality of life, treatment satisfaction, and medication adherence.

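### The CGM analysis aims at predictive value but is set up to report measures of association, which do not directly show how well CGM metrics separate people by pancreatic reserve or insulin resistance

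*Protocol article*

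**What the plan says.** In the protocol article, Study Outcomes states the aim and, in the same sentence, the means: "The study also examines the predictive value of CGM metrics by analyzing their association with pancreatic reserve and insulin resistance". Sample Size and Statistical Analysis gives CGM metrics the same role: "CGM variables will also be examined as potential predictors of pancreatic reserve and insulin resistance". It then names the model, "Depending on whether outcomes are continuous or categorical, linear or logistic regression models will be applied", and the reported quantity, "Results will be expressed as regression coefficients or odds ratios with corresponding 95% CIs". The only criterion stated anywhere is the general one for all analyses, "with a 2-sided *P* value of <.05 considered statistically significant".

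The article names no AUC, sensitivity, specificity, predictive value in the diagnostic sense, R² or internal validation for this analysis. The planned size comes from the primary outcome: "a sample size of 239 participants was estimated".

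**The concern.** An odds ratio or slope says whether the average of the outcome, or its odds, shifts with the CGM metric, and by how much per unit. How well the metric tells one person with low reserve from another with adequate reserve is a different question, and that is the one a reader takes predictive value to mean. With a few hundred participants, an association can be clearly different from zero and still leave the two groups almost wholly overlapping.

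The article does more than stay silent on performance measures. It states a question about prediction, defines the route to it as association, and fixes the quantity to be reported. At stake is the meaning of one secondary result: a metric with near-chance discrimination could be written up as having predictive value, with no reported figure that puts its performance directly in view.

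**Working it through.** **Inputs.** From Sample Size and Statistical Analysis: n = 239; source population N = 1388; expected proportion 25%; margin ±5 percentage points at 95% confidence; two-sided alpha 0.05. The share of participants in each C-peptide class (cut-offs 0.3 and 0.7 nmol/L in Intervention Algorithm) is not given. I take 25% as a working value, with 10% and 50% as a range. These are assumptions: the article's 25% refers to people whose residual function may allow prandial insulin to be stopped, and it is not stated as the share on one side of either cut-off.

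**The plan's own figure.** n0 = z²p(1−p)/d² = 1.96² × 0.25 × 0.75 / 0.05² = 288.1. With finite-population correction, n = 288.1 / (1 + 287.1/1388) = 238.7, so 239. The figure reproduces. It sizes the primary proportion and says nothing about the CGM analysis.

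**Categorical outcome.** For one metric scaled to its within-class SD, the standard error of the log odds ratio is about 1/√(n·p(1−p)). Under the equal-variance binormal model, AUC = Φ(ln OR/√2), and at the cut-point where they are equal, sensitivity = specificity = Φ(ln OR/2).

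At p = 0.25:
- SE = 1/√(239 × 0.1875) = 0.149.
- Just significant: ln OR = 1.96 × 0.149 = 0.293; OR = 1.34; AUC = Φ(0.207) = 0.58.
- Sensitivity = specificity = Φ(0.146) = 0.56. Positive predictive value = 0.558 × 0.25 / (0.558 × 0.25 + 0.442 × 0.75) = 0.30, against a base rate of 0.25.
- Effect detectable with 80% power: ln OR = (1.96 + 0.84) × 0.149 = 0.418; OR = 1.52; AUC = 0.62.

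Over the assumed range of class shares:

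| Share in one class | OR per SD, just significant | AUC | OR per SD, 80% power | AUC |
|---|---|---|---|---|
| 10% | 1.53 | 0.62 | 1.83 | 0.67 |
| 25% (or 75%) | 1.34 | 0.58 | 1.52 | 0.62 |
| 50% | 1.29 | 0.57 | 1.44 | 0.60 |

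For comparison, an odds ratio of 2 per SD gives AUC = Φ(0.693/√2) = 0.69.

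**Check by simulation.** In 1000 data sets with 60 of 239 in one class and a true shift of 0.418 SD, 82% reached P<.05. Among those, the median sample AUC was 0.63 (5th to 95th percentile 0.58 to 0.69). This agrees with the formulas.

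**Continuous outcome.** The smallest significant correlation is r = t/√(n−2+t²), with t = 1.970 on 237 degrees of freedom: r = 1.970/√(237 + 3.88) = 0.127, so R² = 1.6%. At 80% power, r = tanh(2.80/√236) = 0.180, so R² = 3.3%.

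**The case against.** The strongest reply is that the article defines its own term. Study Outcomes says openly that predictive value is examined through association, predictor is ordinary usage for a regression covariate, and Expected Findings speaks only of CGM metrics being related to pancreatic function and insulin resistance. On that reading nothing is contradicted and the wording is merely loose. Performance measures could also sit in an analysis plan that is not shown.

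Part of this stands. The two sections agree on method, and renaming the analysis would be a complete answer. But the article chose a term with a stronger meaning and also fixed the reported quantity, so the mismatch is in the text.

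Several stronger readings are tempting and are not supported:
- *That a weak metric will be declared a predictor.* The article calls the CGM variables potential predictors and has no rule for declaring one. A metric whose true odds ratio is 1.34 per SD would reach P<.05 only about half the time. The right word is could.
- *That nothing else will be reported.* The text does not say so; this would be inferred from the absence of any other measure.
- *That no result could count against a predictive claim.* A confidence interval that includes no effect, or lies close to it, would. A per-SD odds ratio can even be turned into an AUC, as above, but this needs the binormal assumption and SD scaling, and the article does not state the scale.
- *That CGM is being offered as a substitute for C-peptide.* No section proposes this; the treatment decision at visit 1 rests on C-peptide and GADAb.
- *That the results will be overfitted.* The article does not say that metrics are fitted jointly. Time in, below and above range sum to 100%, so all three cannot enter one model with an intercept.

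**Conclusion.** The concern holds as a mismatch between a stated question and a stated measure. At n = 239, meeting the general P<.05 criterion is compatible with an AUC of about 0.58 at a 25% class share (0.57 to 0.62 over shares of 50% to 10%), or with about 1.6% of variance explained. A result of that size would not show useful prediction.

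The AUC figures assume one SD-scaled metric, normal distributions with equal variance in the two classes, the planned sample size with complete data, and the class shares above. The conclusion does not depend on the 25%. The point concerns one secondary analysis and is worth correcting before the data are analysed; it leaves the primary proportion, its confidence interval and the figure of 239 untouched.

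**What to change.** In Sample Size and Statistical Analysis, add to the CGM regression paragraph:
- For categorical outcomes (C-peptide classes defined by the algorithm's 0.3 and 0.7 nmol/L cut-offs, and any categorical insulin-resistance outcome), report the AUC with 95% CI. If a CGM threshold is proposed, report sensitivity and specificity at that CGM threshold. The C-peptide cut-offs define the reference classes and are not the test threshold.
- For continuous C-peptide, HOMA-B or HOMA-IR, report R².
- Where several metrics are fitted jointly, or a threshold is chosen from the data, give bootstrap or cross-validated corrected values.
- Keep coefficients and odds ratios as a description of association, and reserve the term predictive value for the discrimination and R² results.

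If these measures are not wanted, the alternative is to call this an association analysis in both Study Outcomes and Sample Size and Statistical Analysis.

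The cost is small. CGM at visit 1 and C-peptide at inclusion are already in the collection schedule (Table 1), and the Results section places formal analysis after the end of follow-up. The downside is slightly more analysis and figures that look less favourable than odds ratios.
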